## Abstract

**Background:**

Acute severe asthma (ASA) is a leading cause of hospital attendance in children. Standard first-line therapy consists of high-dose inhaled bronchodilators plus oral corticosteroids. Treatment for children who fail to respond to first-line therapy is problematic: the use of intravenous agents is inconsistent, and side effects are frequent. High-flow humidified oxygen (HiFlo) is widely used in respiratory conditions and is increasingly being used in ASA, but with little evidence for its effectiveness. A well-designed, adequately powered randomized controlled trial (RCT) of HiFlo therapy in ASA is urgently needed, and feasibility data are required to plan such an RCT. In this study, we describe the protocol for a feasibility study designed to fill this knowledge gap.

**Objective:**

This study aims to establish whether a full RCT of early HiFlo therapy in children with ASA can be conducted successfully and safely, to establish whether recruitment using deferred consent is practicable, and to define appropriate outcome measures and sample sizes for a definitive RCT. The underlying hypothesis is that early HiFlo therapy in ASA will reduce the need for more invasive treatments, allow faster recovery and discharge from hospital, and in both these ways reduce distress to children and their families.

**Methods:**

We conducted a feasibility RCT with deferred consent to assess the use of early HiFlo therapy in children aged 2 to 11 years with acute severe wheeze not responding to burst therapy (ie, high-dose inhaled salbutamol with or without ipratropium). Children with a Preschool Respiratory Assessment Measure score ≥5 after burst therapy were randomized to commence HiFlo therapy or follow standard care. The candidate primary outcomes assessed were treatment failure requiring escalation and time to meet hospital discharge criteria. Patient and parent experiences were also assessed using questionnaires and telephone interviews.

**Results:**

The trial was opened to recruitment in February 2020 but was paused for 15 months owing to the COVID-19 pandemic. The trial was reopened at the lead site in July 2021 and opened at the other 3 sites from August to December 2022. Recruitment was completed in June 2023.

**Conclusions:**

This feasibility RCT of early HiFlo therapy in children with ASA recruited to the target despite major disturbances owing to the COVID-19 pandemic. The data are currently being analyzed and will be published separately.

**Trial Registration:**

International Standard Randomised Controlled Trial Number Registry ISRCTN78297040; https://www.isrctn.com/ISRCTN78297040

**International Registered Report Identifier (IRRID):**

DERR1-10.2196/54081

## Introduction

### Background

Asthma is a common chronic disorder of reversible airway obstruction characterized by bronchial smooth muscle contraction, airway inflammation, and increased airway secretion [1]. It is the most common noncommunicable disease in childhood, affecting 1 in 10 children worldwide [2] and causing >1000 deaths per day [3]. Children with asthma are prone to episodes of acute severe airway obstruction, characterized by wheezing and increased work of breathing, and often require hospital treatment. Acute severe asthma (ASA) is a leading cause of hospital attendance in children, accounting for up to 7% of all pediatric emergency visits [4] and 8.5% of pediatric admissions from emergency departments (EDs) [5], the most common single cause. Many preschool children who have not yet been diagnosed with asthma are admitted to the hospital with episodes of acute severe wheezing. They present identically and are treated in the same way as older children diagnosed with asthma, although they can be less responsive to therapy [6]. In this paper, the term ASA is used to describe children presenting with acute wheezing and breathing difficulty, whether they have an established diagnosis of asthma.

Therapy for ASA is directed at (1) relieving bronchoconstriction with bronchodilators, (2) decreasing airway inflammation with corticosteroids, and (3) clearing airway secretions so that they do not become thick and block the airways. Standard first-line emergency treatment [7] for ASA in children starts with burst therapy in the first hour (3 doses of high-dose inhaled salbutamol, sometimes with inhaled ipratropium, via a spacer device or nebulizer) and oral corticosteroids. During the next 1 to 4 hours, many children improve clinically and may be discharged. However, some children fail to respond to standard therapy and require hospital admission for more intensive, second-line treatment; without effective treatment, these children are at risk of fatigue, respiratory failure, and death [8]. Second-line treatment commonly includes intravenous bronchodilators (≥1 of aminophylline, salbutamol, and magnesium sulfate). However, evidence for the efficacy of such treatments is limited and inconsistent, with frequent side effects, including tachycardia, jitteriness, tremor, palpitations, nausea, vomiting, elevated lactate level, and hypokalemia [7], which can cause considerable distress to the child and family. Current guidelines [7,9] provide little guidance (because of the scarcity of evidence) regarding which second-line treatment clinicians should use. Therefore, there is a need to investigate other options for treating ASA to improve the effectiveness of the treatment and reduce adverse effects.

High-flow humidified oxygen (HiFlo) therapy is an innovative health care technology that supports breathing by supplying a warm, humidified mixture of air and oxygen at high-flow rates via fine nasal cannulae that has shown promising results in other acute respiratory conditions in children [10]. Traditional oxygen therapy uses cold, unhumidified oxygen directly from a cylinder or a wall outlet. Although this is helpful in improving oxygenation, it is uncomfortable for patients and causes drying and cooling of the nose and mouth, and potentially of the lower airways, which can cause worsening of airway obstruction and even airway damage. Therefore, unmodified oxygen therapy can only be delivered at very low flow rates. Using HiFlo technology, the air or oxygen percentage mix can be varied; it is warmed to body temperature and delivered at 100% humidity. As a result, much higher flows can be delivered without discomfort or adverse effects on the airways.

There is now considerable experience with the use of this technology in both adults and children [10]. Most of the clinical experience and evidence for the efficacy of HiFlo therapy in children is derived from studies performed in preterm neonates with surfactant deficiency. In this population, HiFlo therapy appears to be as effective as continuous positive airway pressure (CPAP) therapy and has become a standard therapy [11]. The physiological basis of its effectiveness is unclear [10,12]: HiFlo therapy itself may generate CPAP [13,14], but it may also reduce nasopharyngeal dead space, reduce upper airway resistance, and reduce the metabolic demand required to humidify inspired gases [15]. In recent years, there has been increased use of HiFlo therapy in infants with acute bronchiolitis [16]. Retrospective studies have suggested that introducing HiFlo therapy for acute bronchiolitis is associated with a reduced need for intubation [17,18]. Prospective trials comparing HiFlo with standard bronchiolitis therapy (low-flow 100% oxygen) have shown improved oxygen saturation levels [19], fewer treatment failures [20,21], and a nonsignificant trend toward faster weaning from oxygen [20]. A Cochrane systematic review concluded that HiFlo therapy is feasible and well-tolerated in infants with bronchiolitis but that further evidence for its effectiveness is needed [22].

To date, there have been no substantial randomized controlled trials (RCTs) of HiFlo therapy in children with ASA, although its use in ASA has been rapidly increasing [23]. The pathophysiology of ASA is very different from that of bronchiolitis. Bronchiolitis is characterized by more mechanical distal airway obstruction [22], whereas in ASA, bronchial smooth muscle constriction plays a major role [1,6]. Retrospective observational studies of HiFlo therapy in children with ASA have suggested improvements in physiological parameters and asthma severity scores [24,25] but have also raised concerns that using HiFlo therapy may delay the initiation of other forms of respiratory support [26]. There have been 2 small single-center pilot RCTs on HiFlo therapy in children with acute asthma. Ballestero et al [27] randomized 62 children with ASA with acute respiratory failure to HiFlo therapy versus conventional oxygen therapy. The asthma score of a higher proportion of children on HiFlo therapy reduced (*pulmonary score*—unreferenced) by 2 points in the first 2 hours of treatment; however, there was no difference in the need for admission or length of hospital stay. Gauto Benítez et al [28] randomized 65 children in a single center in Paraguay to HiFlo therapy or conventional oxygen therapy: the inclusion criteria were somewhat unclear, and both groups received continuous intravenous magnesium in addition to inhaled bronchodilators as a standard practice in this institution. They found no difference in the proportion reducing their asthma score (*pulmonary index score*—again unreferenced) by 2 points or in the length of hospital stay. A recent review of HiFlo in children with ASA by Chao et al [23] concluded that “large well-designed randomized controlled trials assessing the clinical efficacy of high-flow nasal cannula oxygen for children with asthma exacerbation are urgently warranted.” The evidence from published studies is encouraging but mixed and is lacking in clinical outcomes. It does not provide the feasibility information required to plan an RCT on the clinical effectiveness of early HiFlo therapy in childhood ASA.

In summary, ASA in childhood is a common emergency condition with important impacts on health care costs and quality of life and presents a risk to life. HiFlo is a novel therapy that has the potential to treat patients with ASA more effectively and reduce hospital stays and intensive care admissions. However, its use is becoming widespread in clinical practice despite a lack of good evidence. If HiFlo therapy in patients with ASA is not evaluated objectively, there is a risk that a treatment without proven benefits (but with significant costs) may drift into widespread practice. Therefore, there is an urgent need for a well-designed, adequately powered RCT of HiFlo therapy in patients with ASA. To plan such an RCT, feasibility data are required. A definitive RCT would be large and expensive to run, and it is unclear whether it would be feasible, how large it would need to be, and what are the most appropriate outcome measures. This paper presents the protocol of a feasibility study designed to fill this knowledge gap, which has been successfully executed in 4 children’s hospitals in the United Kingdom. The formal results will be published separately.

### Study Aim and Feasibility Objectives

This feasibility study aimed to establish whether a full RCT of early HiFlo therapy in children with ASA can be conducted successfully and safely and whether recruitment to such a trial, using deferred consent, is practicable in children aged 2 to 11 years presenting to the hospital with ASA. The underlying hypothesis is that early HiFlo therapy in children with ASA will reduce the need for more invasive treatments, allow faster recovery and discharge from hospital and, in both these ways, reduce distress to children and their families. The trial was designed to generate the data required to plan a definitive RCT that would satisfy the clinical and health economic end points and the requirements of children, parents, clinicians, and health services.

## Methods

### Primary Feasibility Objectives and Outcome Measures

A total of 6 feasibility objectives and associated outcome measures (Table 1) were established to help determine the feasibility of progressing to a full RCT, which would require the following 4 conditions to be met:

At least 50% enrollment rate among eligible children (feasibility outcome 1)At least 70% deferred consent rate [29] (feasibility outcome 2)At least 80% of data collection is complete per participant for candidate primary outcome measures (feasibility outcome 3)Confirmation that the predicted sample size, number of centers, and recruitment rates would allow an appropriately powered RCT to be conducted in the United Kingdom for 3 years (feasibility outcome 5)

Discussions with colleagues indicated that at least 15 large UK pediatric centers would be interested in participating in a definitive RCT on this question. The study has been discussed with two relevant research networks: (1) the UK National Institute for Health and Care Research (NIHR) Children Respiratory and Cystic Fibrosis Clinical Studies Group and (2) Pediatric Emergency Research in the United Kingdom and Ireland [30], a network of research-active pediatric emergency care clinicians who have indicated that they will facilitate the process of identifying appropriate centers for the definitive study.

The 2 candidate primary outcome measures recorded and evaluated are provided in Textbox 1.

**Table 1 table1:** Primary feasibility objectives and outcome measures.

Feasibility objectives	Feasibility outcome measures	Time point of evaluation
To evaluate enrollment rates	Proportion of enrolled (ie, randomized) children among eligible patients with ASA^a^	Enrollment
To evaluate deferred consent rates	Proportion of children with signed deferred consent among those enrolled into the study	Deferred consent
To assess feasibility of recording candidate primary outcome measures	Proportion of data collection completed per participant for the 2 candidate primary outcome measures	Discharge
To estimate the variability of candidate primary outcome measures	Summary statistics for the 2 candidate primary outcome measures	Discharge
To determine design characteristics for a subsequent definitive study	Proposed design, sample size, and number of centers for a definitive study	End of study
To assess the acceptability of HiFlo^b^ therapy and the deferred consent model to children, parents, and staff	Satisfaction ratings on the end-of-study questionnaire	Discharge

^a^ASA: acute severe asthma.

^b^HiFlo: high-flow humidified oxygen.

Candidate primary outcome measures.Treatment failure needing escalation of therapy as defined in the *Treatment Failure and Escalation* section.The time (h) between presentation to the emergency department and meeting hospital discharge criteria as defined by the following criteria:The ability of the child to maintain arterial oxygen saturation (SpO_2_) measured by pulse oximeter at ≥92% without supplemental oxygen or respiratory support for a 4-hour periodThe ability of the child to remain clinically stable for a minimum of 4 hours between inhaled bronchodilator dosesThe ability to maintain these conditions continuously until hospital discharge

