### Screening

All children arriving at the participating EDs were routinely triaged by an experienced nurse and reviewed clinically during and after completing burst therapy. Children potentially eligible for the study were identified and actively screened for inclusion by ED clinical staff or research nurses according to their local capacity. Screening information included Trust ID number, age, and reasons for not being eligible for trial participation or if they were eligible but declined participation.

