### Deferred Consent and Recruitment

A deferred consent model was used to avoid delay in treatment and minimize distress to families who presented to the ED with acutely unwell children. The consent process is summarized in this section (complete details are provided in section 6.4 of the study protocol in Multimedia Appendix 1).

Informed consent was not sought before randomization, but the parents were approached for informed consent within a maximum of 72 hours of randomization once their child’s condition was stable. The parents were approached for informed consent by trained staff from the direct care team, who explained the study and provided information sheets to the parents and children (if age appropriate). The parents were given time to read and understand the information and the opportunity to clarify any questions regarding the study and their child’s participation. Written informed consent was obtained from all the parents.

If a child was discharged from hospital before parents could be approached for deferred consent, they were contacted by a trained research nurse who explained the study via phone. Written participant information and consent forms were then sent out by post. This model was successfully used, for example, in the Emergency treatment with levetiracetam or phenytoin in status epilepticus in children (EcLIPSE) study by Lyttle et al [52], and feedback from parents was positive [37]. There was a possibility for parents to provide verbal consent via phone in special circumstances. A special process for the sensitive case of having to approach bereaved parents for consent was designed.

If neither written nor verbal consent was received, the child was not recruited into the study, and the data collected were not included in the study analysis.

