We used an asthma scoring system and selected PRAM because it was the only asthma scoring system validated across the entire age range of 2 to 11 years. At least 17 different asthma severity scores have been published, but few EDs in the United Kingdom regularly use any of them as part of routine clinical practice [56], and only one of our sites had any prior familiarity with PRAM. The study protocol used the PRAM score in 2 ways: as one of the entry criteria (PRAM score ≥5 after first-line treatment) and as a candidate (secondary) outcome measure (time to achieve a PRAM score of ≤3). As noted above, implementing PRAM at the study sites and maintaining PRAM competency, despite high staff turnover, required considerable input of training resources. The advantage of using a validated asthma score as an entry criterion was that it standardized the severity of acute asthma in children entering the study, allowed comparison with other acute asthma trials [36], and allowed us to stratify randomization by asthma severity at entry. A potential disadvantage was that it risked reducing out-of-hours recruitment owing to PRAM-trained staff not being available.

As with many clinical trials since 2019, the conduct of this study was severely affected by the COVID-19 pandemic. It was necessary to pause recruitment for a prolonged period because of general logistic issues affecting all clinical research and specific concerns relating to the theoretical risks of aerosol generation and COVID-19 transmission from HiFlo therapy. The experience gained by the research team (both in adapting trial procedures and disseminating new research findings on aerosol generation) to allow the successful completion of the trial will be valuable in planning a definitive RCT.

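### The 70% deferred-consent threshold counts signed consent only, while the consent procedure also accepts verbal consent

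*Protocol article*

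**What the plan says.** The section Primary Feasibility Objectives and Outcome Measures makes progression depend on four conditions. The second is a deferred-consent rate of at least 70%. Table 1 gives the measure behind it: "Proportion of children with signed deferred consent among those enrolled into the study". The first row of the same table equates enrolled with randomized, so the denominator is all randomized children.

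The section Deferred Consent and Recruitment makes three statements that bear on the numerator:

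- On the route to consent: "There was a possibility for parents to provide verbal consent via phone in special circumstances".
- On inclusion: "If neither written nor verbal consent was received, the child was not recruited into the study". The same sentence removes such a child's data from the analysis.
- On what happened: "Written informed consent was obtained from all the parents".

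Study Design and Setting says that treatment was not blinded. Parents were approached after randomization, within 72 hours at most. Subgroup Analyses and Participant Population describes the analysis as intention-to-treat among recruited participants whose consent was received.

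**The concern.** The rule that admits a child to the analysis and the rule that counts the child as a consenter are different. Under the inclusion rule, verbal consent is enough. Under Table 1 it is not. A child whose parent agreed by telephone and returned no form would supply outcome data and at the same time count against the 70% threshold. The third statement, that consent was written for all parents, agrees with neither the telephone route nor an inclusion rule that names verbal consent, unless each verbal consent was later confirmed in writing. The article does not say that it was.

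The threshold is one of four conditions for a definitive trial, so the count behind it should be unambiguous. A second, smaller matter belongs with it. Consent was asked of parents who could already know which treatment their child received, and children without consent leave the analysis. A single pooled rate cannot show whether that loss differed between arms, and a definitive trial using the same consent model would need to know.

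**Working it through.** **Inputs from the article.** Threshold 70%. Denominator: randomized children (Table 1). Planning attrition to deferred consent 30%, original target 70, revised target 48 (Sample Size and Planned Recruitment Rate). Study size 50 (Study Design and Setting; Discussion). Equal allocation between arms.

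**Inputs that the article does not give, assumed here.** The number randomized, the true rate of any valid consent (p), and the share of consents that stayed verbal only (s, taken as 0 to 20%).

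**1. The plan's own figure.** 70 × (1 − 0.30) = 49, against the 50 recommended. In reverse, 50 / 0.70 = 71.4, against 70 stated. The original target is reproduced to within two children, and it shows that 70% consent was the planning value as well as the pass mark.

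**2. Pass mark and the effect of verbal-only consents.** The pass mark is the smallest whole number m with m / N ≥ 0.70. The last three columns take exactly m valid consents and apply the signed-only count.

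| N randomized (assumed) | 0.70 × N | m | all signed | 1 verbal only | 2 verbal only |
|---|---|---|---|---|---|
| 48 | 33.6 | 34 | 34/48 = 70.8% | 33/48 = 68.8% | 32/48 = 66.7% |
| 50 | 35.0 | 35 | 35/50 = 70.0% | 34/50 = 68.0% | 33/50 = 66.0% |
| 70 | 49.0 | 49 | 49/70 = 70.0% | 48/70 = 68.6% | 47/70 = 67.1% |

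At the pass mark, one verbal-only consent is enough to turn a pass into a fail.

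**3. If 48 or 50 are consented children instead.** The consent section uses recruited to mean consented, so 48 may be a count after consent. For the threshold to be met, at most 48 / 0.70 = 68.6, so 68, or 50 / 0.70 = 71.4, so 71, could then have been randomized. At those limits one verbal-only consent gives 47/68 = 69.1% or 49/71 = 69.0%, again below 70%. The conclusion does not depend on which reading is right.

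**4. Verbal share needed to reverse the result.** The signed-only rate is p × (1 − s). It falls below 0.70 when s > 1 − 0.70/p:

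- p = 75%: s above 6.7%
- p = 80%: s above 12.5%
- p = 85%: s above 17.6%
- p = 90%: s above 22.2%

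**5. Chance of passing.** P(X ≥ m), with X binomial (N, p(1 − s)) and p = 80%:

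| N, m | s = 0 | s = 5% | s = 10% | s = 20% |
|---|---|---|---|---|
| 48, 34 | 0.956 | 0.843 | 0.641 | 0.203 |
| 50, 35 | 0.969 | 0.875 | 0.688 | 0.233 |

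**6. Direction.** Signed consents are a subset of valid consents, so the signed-only rate can never exceed the rate of valid consent. The error runs toward a fail only.

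**7. What pooling can hide.** Assume 24 per arm and 34 consents in all. The pooled rate is 34/48 = 70.8% whether the split is 17 and 17 (17/24 = 70.8% in each arm) or, at the extreme, 24 and 10 (100% and 10/24 = 41.7%). This is a bound, not an expectation.

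**The case against.** Verbal consent was meant for exceptional cases, and the article reports written consent from all the parents. If each verbal consent was later confirmed on paper, the two counts are identical and nothing changes. The article also refers to section 6.4 of the full protocol for the details of consent, and that section may settle the matter. Both points stand: they may reduce the numerical effect to zero. They do not remove the conflict between the three statements as printed.

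On reporting by arm, the article already plans a CONSORT flowchart and descriptive analysis by trial arm, and says openly that only consented children are analysed. That is fair. Consent by arm is a useful addition, not the repair of a contradiction.

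A reader might infer that three of the four thresholds rest on contradicted counts. The documents do not support this for the other two.

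- **Enrollment (50%).** Table 1 defines the ratio clearly. Children were "actively screened for inclusion by ED clinical staff or research nurses according to their local capacity", which can describe which staff did the screening and need not mean that children were missed. The article also says that all arriving children were triaged and reviewed, that PRAM scoring before randomization was treated as standard care with an adapted process where the pathway was not in use, and that screening logs will be examined. The Discussion concedes of the PRAM entry criterion that "it risked reducing out-of-hours recruitment owing to PRAM-trained staff not being available". This is a disclosed limit on capture, of unknown size. Applying 50% to a denominator that adds every child without a PRAM score would be wrong, since many of those children may have responded to first-line treatment and so been ineligible.
- **Completeness (80%).** The condition reads "At least 80% of data collection is complete per participant for candidate primary outcome measures". One could argue that with two outcomes a child can score only 0, 50 or 100%, but that assumes one yes/no field per outcome. Both outcomes have several recorded components, so 80% per child is attainable. What the article does not state is how the per-child figures become one trial-level result, which may be left to the full protocol or the SAP.

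**Conclusion.** The concern holds for the consent threshold alone. Table 1 counts signed consent, the consent procedure accepts written or verbal consent, and a third statement says that all consent was written. The three must be reconciled.

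The size depends on unreported counts. It is nil if no child was included on verbal consent alone. Otherwise each such child lowers the rate by one Nth, which is 1/48 = 2.1 percentage points if 48 were randomized. At the pass mark, a single child decides the result. With 50 randomized, true consent of 80% and an assumed 10% verbal-only share, the chance of meeting the threshold falls from 0.969 to 0.688.

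A reader might conclude that progression could be passed or failed wrongly. For this count only a wrong fail is possible.

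**What to change.** 1. Define the numerator as all children with valid consent, written or verbal, and the denominator as all randomized children. Apply the 70% threshold to that ratio.
2. Show the signed-only count beside it.
3. Reconcile the statement that all consent was written: either verbal consents were later signed, or some children were included on verbal consent and their number is given.
4. Report the consent rate by randomized arm.
5. State whether 48 and 50 are randomized or consented children.

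The cost is a change of wording and one extra tabulation from data that the trial already holds. The article says that the data were still being analysed, so this can be done before the results are reported.

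Two optional additions on the other thresholds: give the number of children not screened or without a PRAM score beside the logged enrollment rate, without applying the 50% threshold to it, and state how per-participant completeness becomes one trial-level pass or fail.
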